##### Radiological Outcome

X-rays will be obtained as per standard hospital protocol at 6 and 12 weeks as well as 1 year after injury. The final radiological outcome will be determined 1 year after injury and will include union, radial inclination, volar tilt, carpal alignment, ulnar variance, and the presence and size of any step or gap in the articular surface.

### Timeline and Recruitment

The recruitment procedure is visualized in Figure 1. The follow-up schedule for the patients and time point for the assessment of each outcome are listed in Table 1.

**Figure 1 figure1:**
[figure not shown]
Flowchart of Patient Selection.

**Table 1 table1:** Outcome measures.

	First presentation	6 weeks	12 weeks	1 year	2 years
Outpatient clinic		✓	✓	✓	
X-ray	✓	✓			
PRWE^a^	✓		✓	✓	✓
PASE^b^	✓		✓	✓	✓
NRS^c^ pain		✓	✓	✓	✓
ROM^d^			✓		
EQ-5D-5L	✓		✓	✓	✓
Complications		✓	✓	✓	✓
Living situation	✓	✓	✓	✓	

^a^PRWE: Patient-Rated Wrist Evaluation.

^b^PASE: Physical Activity Score for the Elderly.

^c^NRS: Numerical Rating Scale.

^d^ROM: range of movement.

### Data Collection

In every participating institution, a project leader will fill in all the patient information in the secure web-based database on REDCap (Research Electronic Data Capture; Vanderbilt University). The original data will be collected from the institution’s electronic patient records, the picture archiving and communication system, the different questionnaires, and pseudonymized prior to entry in the database.

Health care workers from the participating institutions will get access to REDCap, which enables centralized tracking of potentially eligible patients in compliance with the good clinical practice guidelines for electronic data collection. Every 2-4 weeks, this list of patients will be screened by the project leader, and explanatory and response variables will be entered on the study website. All data will be saved in a research folder that can only be accessed by the principal investigator and the project leader or leaders.

### Sample Size Calculation

This study will be a noninferiority study, for which we assume that conservative treatment in older patients with a distal radius fracture is noninferior to operative treatment. The reason for choosing a noninferiority design is as follows. Operative treatment for distal radius fractures inherently exposes patients to additional risks of operation-related complications and costs. This is not the case for conservative treatment. If the study would demonstrate that both treatments are equal with regard to the primary outcome, it would automatically imply that patients should be treated with the lesser invasive treatment of the 2 (in this case, conservative treatment).

The sample size is based on the minimal important clinical difference of the PRWE score, which is 11.5 points (with an average SD 14). Using the minimal important clinical difference (11.5 points) as the noninferiority margin, a statistical significance threshold (α) of 5%, and a power of 90%, 32 patients per group are needed [14]. Taking into account a 30% loss to follow-up (due to the considerable age of the included study population), a total of 92 patients will have to be included, with at least 46 patients in each treatment group.

### Statistical Analysis

The statistical software package SPSS (IBM Corp) will be used for analysis. All analyses will be performed according to the intention-to-treat principle. Multiple imputation will be used for missing values. Depending on their distribution, baseline characteristics will be described as means and SDs or median and IQR for continuous variables. Categorical variables will be reported as counts and percentages. Treatment groups will be compared using an independent Student *t* test (2-tailed) or chi-square test, as appropriate.

The primary outcome will be analyzed using a regression analysis with the 12 weeks PRWE score as dependent and treatment as independent variable. Potential confounders (notably age and fracture type) will be included as covariates in the model. Regression coefficients will be calculated with corresponding 95% CI. Regression analysis will also be used for analyzing the secondary outcomes with correction for the previously mentioned confounders.

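### A noninferiority claim is confined to intention-to-treat, with no rule for casts later converted to surgery and no supportive analysis

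*Protocol article*

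**What the plan says.** Under Sample Size Calculation the article states the aim: "This study will be a noninferiority study". The direction is that nonoperative treatment is noninferior to operative treatment, and the margin is fixed: "Using the minimal important clinical difference (11.5 points) as the noninferiority margin". The reason given for the design is that "If the study would demonstrate that both treatments are equal with regard to the primary outcome, it would automatically imply" use of the less invasive option.

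Under Statistical Analysis the analysis set is fixed without exception: "All analyses will be performed according to the intention-to-treat principle". The primary analysis regresses 12-week PRWE on treatment with covariates, notably age and fracture type, and "Regression coefficients will be calculated with corresponding 95% CI". That section mentions neither noninferiority nor the margin, and it names no per-protocol or as-treated analysis.

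Three other sections bear on the point:
- Intervention: the treating surgeon chooses the treatment, and it begins before the patient is approached.
- Expert Panel: the treating physician's initial plan is carried on.
- Complications: adverse events that need surgery are recorded at each outpatient visit and at 2 years. No rate of conversion from cast to surgery is given, nor a rule for the group in which a converted patient is analysed.

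**The concern.** In a superiority trial, crossover under intention-to-treat usually pulls the estimate toward zero and makes the claim harder to reach. In a noninferiority trial the same pull makes the claim easier. A cast patient who is operated on before week 12 stays in the nonoperative group but may bring a result partly produced by surgery.

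Intention-to-treat normally rests on a randomized assignment, and here there is none. The starting treatment is the natural substitute, but the article does not say so. A patient put in a cast at presentation and operated on a few days later could be placed in either group.

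Because the text covers all analyses, relying on intention-to-treat alone is a stated choice and not a detail left open. The article attaches a treatment recommendation to the result, so a false claim of noninferiority would carry into practice.

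**Working it through.** **Inputs from the article (Sample Size Calculation).** Margin 11.5 PRWE points, SD 14, α 5%, power 90%, 32 per group, 30% loss, 46 per group and 92 in total. Sidedness and the assumed true difference are not stated.

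**Step 1: reproduce the plan's figure.** With one-sided 2.5% (the upper limit of a two-sided 95% CI) and a true difference of 0:

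n = 2 × 14² × (1.960 + 1.282)² / 11.5² = 31.1, rounded up to 32 per group.

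32 / 0.70 = 45.7, rounded up to 46 per group, 92 in total. Both figures reproduce. One-sided 5% would give 26 and does not. The sizing therefore corresponds to comparing one limit of the 95% CI with 11.5. Power under that rule with 32 per group is 89.9% (noncentral t).

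**Step 2: dilution under intention-to-treat.** Let D be the true PRWE difference (nonoperative minus operative), c the share of casts converted before week 12, and k the share of the operative advantage that converted patients gain by week 12. Then

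ITT difference = D × (1 − c × k).

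The documents give neither c nor k. Both are assumptions here.

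**Step 3: chance of a false noninferiority claim when D = 11.5.** The standard error with 32 per group is 14 × √(2/32) = 3.5. In the normal approximation the chance is Φ((11.5 − ITT difference)/3.5 − 1.96). For c = 0.10 and k = 1, the ITT difference is 10.35 and Φ(0.329 − 1.96) = 5.1%. For c = 0.20 and k = 1, it is 9.2 and Φ(0.657 − 1.96) = 9.6%. The noncentral t distribution, unadjusted for covariates, gives:

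| Conversion c | ITT difference (k = 1) | False claim, 32 per group | False claim, 46 per group |
|---|---|---|---|
| 0% | 11.5 | 2.5% | 2.5% |
| 10% | 10.35 | 5.1% | 5.8% |
| 20% | 9.2 | 9.5% | 11.9% |
| 30% | 8.05 | 16.1% | 21.5% |

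More complete follow-up does not help: the diluted difference lies below the margin, so a larger sample makes the false claim more likely.

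**Step 4: how far the result depends on k.** At 20% conversion and 32 per group:

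| k | Meaning | ITT difference | False claim |
|---|---|---|---|
| 1 | full operative result | 9.2 | 9.5% |
| 0.5 | half the advantage | 10.35 | 5.1% |
| 0 | no better than cast | 11.5 | 2.5% |
| −0.5 | worse than cast | 12.65 | 1.1% |

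The direction of the bias therefore depends on how converted patients fare by week 12.

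**Step 5: would a per-protocol set be safer?** Suppose 20% of casts convert, and the tendency to convert correlates 0.3 to 0.5 (assumed) with the PRWE the patient would have had in a cast. Dropping them lowers the cast-group mean by 14 × r × φ(0.842)/0.80 = 14 × r × 0.350, which is 1.5 points at r = 0.3 and 2.4 at r = 0.5. The dilution in Step 2 at 20% and k = 1 is 11.5 − 9.2 = 2.3 points. The two biases can be of similar size, and both can favour nonoperative treatment.

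**The case against.** The strongest defence is that comparing starting strategies, with later surgery counted as part of the nonoperative strategy, is a sensible practical question, and intention-to-treat answers it. This stands, and it is why intention-to-treat should remain the primary analysis.

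The size is also open to challenge. No conversion rate is documented, and a fracture operated on late has had less time to recover by week 12, so converted patients may score no better than cast patients, or worse. Step 4 shows that the inflation then vanishes or reverses. This stands too. The bias toward noninferiority is plausible but not certain.

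A per-protocol set removes failed casts and has a selection bias of its own. Age and fracture type, the covariates named, do not measure redisplacement. It follows that requiring success in both sets would not guarantee protection, so the second analysis should be supportive only.

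A reader might go further and infer, from the word equal and the 2-tailed t test, that a non-significant difference will be taken as noninferiority. The article does not support that. No section states such a rule, the t test follows the description of baseline characteristics, and the primary outcome has its own regression with a 95% CI. The margin is set and the sample size is a correct noninferiority calculation. What is absent is one sentence linking the interval to the margin. That, with the loose word equal, is mostly a matter of drafting.

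**Conclusion.** The point holds in a limited form. The article fixes intention-to-treat for every analysis of a noninferiority claim, leaves the group of converted patients undefined in a non-randomized study, and names no supportive analysis.

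If converted patients reach the operative result by week 12 and the true difference equals the margin, the false-claim rate with 32 per group goes from 2.5% to about 5% at 10% conversion and 9.5% at 20%. This rests on assumed conversion rates, SD 14 and an unadjusted comparison. If converted patients gain nothing there is no inflation, and if they do worse intention-to-treat works against the claim. That uncertainty is a reason to prespecify a second view of the data. It does not show that the primary analysis is wrong.

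**What to change.** In Statistical Analysis:
1. Define the intention-to-treat group as the treatment first started, and state that patients converted later stay in that group.
2. Add a prespecified supportive per-protocol or as-treated analysis of 12-week PRWE with covariate adjustment, reported beside intention-to-treat. State that any disagreement between the two limits the noninferiority conclusion.
3. State that noninferiority is concluded only if the upper limit of the two-sided 95% CI for adjusted PRWE (nonoperative minus operative) is below 11.5.

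In Sample Size Calculation, replace equal with noninferior within 11.5 points.

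The cost is a few sentences and one more model. The sample size stays at 92, because the confidence-limit rule is the one that 32 per group reproduces. Surgery for adverse events is already recorded, but redisplacement is not named there, so the team should confirm that every conversion and its date are captured. The supportive set has its own selection bias because it drops failed casts. It therefore supports intention-to-treat and does not replace it.

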## Methods

### Study Design

Although randomized controlled trials are generally considered the gold standard to investigate the effects of medical treatments, both patients and surgeons can have a strong preference for a certain treatment, which may limit the feasibility of a randomized controlled trial and therefore the generalizability of its results [4,5]. Provided possible incomparability of patients who receive different treatment modalities (ie, confounding) is adequately controlled for, observational studies could provide an alternative source of information.

A natural experiment design uses existing variation in treatment allocation (eg, due to practice variation). Natural experiments are observational studies in which treatment allocation is determined by factors outside the control of the investigators but also (to a large extent) independent of patient characteristics [6,7]. We assume the decisions regarding the treatment of distal radius fractures are largely influenced by the training of the treating surgeons. Since patients with a distal radius fracture generally visit the nearest hospital, treatment allocation is dependent on which surgeon is on call, which is likely independent on patient characteristics. Hence, the process governing treatment allocation arguably resembles that of randomization. Practice variation therefore provides an opportunity to conduct a natural experiment of the effect of operative versus nonoperative treatment of distal radius fractures. In order to further minimize the influence of patient characteristics on treatment decisions, a selection could be made of those patients for whom a panel of physicians disagree regarding the preferred treatment option (ie, for whom there clearly is a clinical equipoise). For these patients, both operative and nonoperative treatment of distal radius fractures are viable, and treatment choice is predominantly determined by personal or local preference.

This study is an international multicenter prospective observational cohort study for which patients will be identified after treatment has been initiated. Outcome data will be prospectively collected. Patients will be recruited from 5 hospitals in countries with a predominant preference for operative (Switzerland) and nonoperative treatment (the Netherlands).

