### Expert Panel

Following the identification of eligible patients and obtainment of informed consent, anonymous radiographs including key images of computer tomography scans if available, and baseline characteristics including information regarding comorbidities and activity levels (details below) will be made available on a secure web-based platform. This will allow the members of the panel to reach a “clinical” decision regarding their treatment recommendation. The panel will be blinded to the actual treatment received and the origin of the case.

The comorbidities, which will be reported to the experts, are cardiomyopathy including valvular disease, history of stroke or other brain injury with persistent neurological deficit, diabetes mellitus, cardiovascular disease, active malignancy, rheumatoid arthritis, and history of alcohol or drug abuse.

Additionally, the experts will be provided with information regarding the usage of the following medications: anticoagulant agents (vitamin K antagonists and new oral anticoagulants), immunosuppressants, and current chemotherapy.

The activity levels are independent, independent with support from family or district nurse or nursing home, and use of a walking aid prior to injury (no, walking stick, frame, and not mobile).

The expert panel will consist of 3 representatives from each “school.” All panel members will be certified trauma surgeons. Half of them are generally in favor of conservative treatment (“school A”), while the others are generally in favor of operative treatment (“school B”). Patients will ultimately be included in the study if clinical equipoise is achieved, meaning 2 or more of the experts disagree with the rest of the panel. This is expected to result in 2 comparable groups for which clinical equipoise exists. The actual treatment the patient receives will continue as initially planned by the treating physician (see below).

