### Intervention

The decision whether operative or nonoperative treatment is chosen is left to the treating trauma surgeon as per the local standard of the participating hospital. Treatment will be initiated before the patient is approached for recruitment. Nonoperative treatment will consist of immobilization in a below the elbow cast for 4-6 weeks with or without prior closed reduction.

Operative intervention will be based on the treating surgeon’s experience and preference. It will consist of open reduction and internal plate fixation using volar, dorsal, spanning or a combination of plates, or reduction (open or closed) and fixation with an external fixator with or without Kirschner wires. The participating hospitals in Switzerland will use the 2.4-mm distal radius plate system (Arthrex) for internal plate fixation. Perioperative management including anesthesia, antibiotics, and thromboembolism prophylaxis will follow the national guidelines. Postoperative care and immobilization will be decided by the treating surgeon. When possible, functional aftercare without immobilization will be allowed. Physiotherapy will be provided according to the local standards.

All patients (operative and nonoperative) will be reviewed in the outpatient clinic at 6 and 12 weeks as well as 1 year after treatment or surgery. In addition, patients will be contacted by phone 2 years after treatment or surgery.

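### The primary regression names only age and fracture type; the panel vote and first-presentation PRWE should be named in advance, because a risk of residual confounding in either direction remains

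*Protocol article*

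**What the plan says.** All references are to the protocol article.

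- **Statistical Analysis.** The primary analysis is a "regression analysis with the 12 weeks PRWE score as dependent and treatment as independent variable". On covariates: "Potential confounders (notably age and fracture type) will be included as covariates in the model". For the rest: "Regression analysis will also be used for analyzing the secondary outcomes with correction for the previously mentioned confounders". No other covariate is named anywhere in the article.
- **Table 1.** PRWE, PASE, EQ-5D-5L and living situation are all ticked at first presentation.
- **Expert Panel.** Six surgeons, three from each school, give a recommendation on every candidate case, blinded to the treatment received and to the case's origin. They see radiographs, and "baseline characteristics including information regarding comorbidities and activity levels (details below) will be made available on a secure web-based platform". A case enters the study on disagreement, "meaning 2 or more of the experts disagree with the rest of the panel".
- **Intervention.** "The decision whether operative or nonoperative treatment is chosen is left to the treating trauma surgeon as per the local standard".
- **Study Design.** Observational evidence is presented as an alternative to randomisation on a condition: "Provided possible incomparability of patients who receive different treatment modalities (ie, confounding) is adequately controlled for". The same section notes that "patients will be identified after treatment has been initiated". The Discussion expects confounding to be minimal and offers multivariable analysis in addition.

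**The concern.** The comparison is not randomised, so the choice of covariates is part of the argument for its validity. The equipoise filter narrows the range of cases but leaves a gradient: with six voters and at least two dissenters, included cases have 2, 3 or 4 votes for surgery. If cases with more votes are operated on more often, and if the vote also carries information about 12-week PRWE, the treatment coefficient absorbs part of that difference. The vote is the one variable that summarises, blind to treatment, how strongly a case points towards surgery. It exists for every included patient, yet the model description does not name it.

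Two smaller matters go with this. The baseline value of the outcome is not named either, and it is the usual source of extra precision. The secondary models refer back to the same confounders, so PASE, EQ-5D-5L and 1-year PRWE are not explicitly adjusted for their own first-presentation values. An open list also leaves room to choose covariates after outcomes are known, which is undesirable in a noninferiority comparison.

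**Working it through.** **1. The plan's own figure.** Inputs from Sample Size Calculation: margin 11.5, SD 14, alpha 5% (sides not stated), power 90%, 30% loss.

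n per group = 2 × [14 × (1.960 + 1.282) / 11.5]² = 31.1, so 32. This treats the 5% as two-sided, which is 2.5% one-sided and matches the 95% CI in Statistical Analysis. A one-sided 5% would give 26. Then 32 / 0.7 = 45.7, so 46 per group and 92 in total. The stated figures reproduce, with no covariate adjustment in them.

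At 32 per group, SE = 14 × √(2/32) = 3.5, the CI half-width is 1.96 × 3.5 = 6.86, and power is Φ(11.5/3.5 − 1.96) = 90.8%.

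**2. Precision from first-presentation PRWE.** Its correlation r with 12-week PRWE is not in the article, so r is an assumption. Residual SD = 14 × √(1 − r²).

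| Assumed r | Residual SD | CI half-width | CI narrower by | Power at 32 per group |
|---|---|---|---|---|
| 0 | 14.00 | 6.86 | – | 90.8% |
| 0.1 | 13.93 | 6.83 | 0.5% | 91.0% |
| 0.3 | 13.36 | 6.54 | 4.6% | 93.1% |
| 0.5 | 12.12 | 5.94 | 13.4% | 96.7% |

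**3. Bias from an omitted factor such as the vote.** Bias = imbalance between groups (in SDs of the factor) × its correlation with 12-week PRWE × 14. Both inputs are assumptions. For scale, if votes 2, 3 and 4 were equally common their SD would be √(2/3) = 0.82, so an imbalance of 0.5 SD would be about 0.41 votes.

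| Imbalance (SD) | Correlation | Bias (points) | Share of margin | One-sided error at the margin, if bias favours nonoperative | Power at true difference 0, if bias runs the other way |
|---|---|---|---|---|---|
| 0.2 | 0.1 | 0.28 | 2.4% | 3.0% | 89.4% |
| 0.2 | 0.3 | 0.84 | 7.3% | 4.3% | 86.1% |
| 0.5 | 0.3 | 2.10 | 18.3% | 8.7% | 76.6% |
| 0.5 | 0.5 | 3.50 | 30.4% | 16.9% | 62.8% |

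Error = Φ(bias/3.5 − 1.96), against a nominal 2.5%. Power = Φ((11.5 − bias)/3.5 − 1.96).

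**4. Direction.** Higher PRWE is worse. If votes for surgery mark worse fractures, the operated group has the poorer prognosis and nonoperative treatment looks better than it is. But the panel also sees comorbidities, medication, independence and walking aids. Votes for surgery may then mark fitter patients, and the bias runs against noninferiority. The article does not settle which.

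**5. Cost of adjusting for the vote.** If the vote correlates r with treatment, the variance of the treatment coefficient is multiplied by 1/(1 − r²): 1.10 at 0.3 and 1.33 at 0.5. Suppose the vote explains none of the outcome variance left after PRWE. Then a vote–treatment correlation of 0.3 exactly cancels the gain from PRWE at r = 0.3, since (1 − 0.09) × 1/(1 − 0.09) = 1. The vote is therefore a control for bias, and it need not add precision.

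**The case against.** The strongest reply is that nothing has been shown to be left out. The word *notably* marks examples, the article is condensed, and a fuller covariate list may stand in an analysis plan that is not shown. That is correct: a reader might infer that the vote and baseline PRWE are excluded, and the text does not say so. What remains is that the article names two covariates, carries the mentioned confounders over to the secondary outcomes, and does not name the two variables best suited to its own design.

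Second, adjustment is not the main protection. Allocation by local practice and restriction to cases on which a blinded panel disagrees come first, and the Study Design section attributes the treatment decision largely to surgeon training and to who is on call. This also stands. If allocation works as described, the vote will hardly correlate with treatment, and adjusting for it will cost almost nothing. A reader might infer that confounding by indication is present and flatters nonoperative treatment; the documents show neither its presence nor its direction.

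Third, first-presentation PRWE may not be a clean baseline. Patients are identified after treatment has started, and the article does not say whether the score refers to pre-injury status. If treatment could already have affected it, adjusting for it could add bias. With 82 patients already consented (23 in Switzerland, 59 in the Netherlands), new wording cannot change how their scores were recorded. This objection stands and limits the recommendation.

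**Conclusion.** The point holds as a recommendation to name the covariates in advance, with the panel vote first among them. The open list names only age and fracture type, treatment is chosen by the surgeon, and the 2-to-4 vote range leaves a gradient of indication inside the included sample. A risk of residual confounding follows, of unknown size and in either direction. If it favours nonoperative treatment, it favours the noninferiority claim.

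The bias figures of 0.28 to 3.5 points rest wholly on assumed imbalances and correlations and show scale only. The precision gain from PRWE is likewise conditional on an assumed correlation. A reader might infer that without baseline adjustment the study falls short of its power; it does not, because the stated 32 per group and 90% power reproduce without any covariate.

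**What to change.** Before any outcome analysis, specify the primary model as 12-week PRWE on treatment, number of panel votes for surgery (2, 3 or 4), age, fracture type and first-presentation PRWE, or give a reason for omitting any of these. For each secondary score, use its own first-presentation value where Table 1 collects one (1-year PRWE, PASE, EQ-5D-5L).

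State what the first-presentation PRWE refers to and when it was recorded. Keep it in the primary model only if it reflects pre-injury status, or was recorded in the same way in both groups before treatment could affect it. Otherwise use it in a sensitivity analysis. The same check suits the other first-presentation questionnaires.

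The cost is analysis wording, a few degrees of freedom, and some variance inflation if the vote correlates with treatment (about 1.10 at 0.3, 1.33 at 0.5). That inflation is material only when the vote is related to treatment, which is also when adjustment may be needed. No new variable has to be collected, but how PRWE was recorded for patients already enrolled must be checked.

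### The covariates named for the 1-year radiological outcomes do not include the deformity at first presentation; naming it would guard against residual imbalance and improve precision

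*Protocol article*

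**What the plan says.** All of the following is in the Methods of the protocol article.

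- **Primary model (Statistical Analysis).** The 12-week PRWE is regressed on treatment, and "Potential confounders (notably age and fracture type) will be included as covariates in the model".
- **Secondary outcomes (same section).** "Regression analysis will also be used for analyzing the secondary outcomes with correction for the previously mentioned confounders". No outcome-specific baseline value is mentioned.
- **Radiological Outcome.** "The final radiological outcome will be determined 1 year after injury and will include union, radial inclination, volar tilt, carpal alignment, ulnar variance", followed by the presence and size of an articular step or gap. The section speaks only of final values and does not say that the same parameters are measured at presentation.
- **Baseline films.** Table 1 ticks an X-ray at first presentation. Under Expert Panel, the panel receives "anonymous radiographs including key images of computer tomography scans if available". Under Data Collection, the picture archiving system is a data source.
- **Allocation.** The Intervention section describes the choice of treatment thus: "The decision whether operative or nonoperative treatment is chosen is left to the treating trauma surgeon as per the local standard of the participating hospital". Patients are approached only once treatment has begun.

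**The concern.** One covariate set, introduced for a patient-reported score at 12 weeks, is applied to anatomical measurements at 1 year. For an alignment measurement, the same parameter before treatment is an obvious prognostic covariate, and the named set does not contain it.

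The design gives this some weight:

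- The treating surgeon sees the displacement when choosing treatment.
- Eligibility sets no displacement criterion, so only the panel narrows the range. The panel admits a 4:2 split in either direction, so included fractures can still vary in displacement.
- Casting may be done with or without closed reduction, so some initial deformity can plausibly persist to 1 year.

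If displacement differs between the groups, part of the 1-year difference would reflect how the fractures started and not what treatment did. Radiological outcome is part of the study aim stated in the Introduction, so the comparison will be read. Separately, leaving out a prognostic baseline value costs precision in a study planned on 32 evaluable patients per group.

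**Working it through.** **1. The plan's own figure.** With margin 11.5, SD 14, true difference 0, power 90% and two-sided 5% (one-sided 2.5%):

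n = 2 × (1.960 + 1.282)² × 14² / 11.5² = 31.1, so 32 per group. Then 32 / 0.70 = 45.7, so 46 per group and 92 in total.

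This matches Sample Size Calculation. It concerns the PRWE only and is used here just to set n at 32 (after the planned loss) or 46 (no loss).

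**2. Inputs that the documents do not give (assumed).**

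- rho, the within-group correlation of the first-presentation value with the 1-year value: 0.3 to 0.7.
- d, the systematic difference between groups in the first-presentation value, in SD units: 0, 0.2 or 0.5.
- For simplicity, what age and fracture type already explain is ignored and one slope is used for both groups.

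**3. Formulas** (1-year value in SD units, no true treatment effect).

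- Bias when the baseline value is left out = rho × d.
- SE of the group difference = √(2/n), which is 0.25 at n = 32.
- Chance of a false positive at two-sided 5% = 1 − Φ(1.96 − bias/SE) + Φ(−1.96 − bias/SE).
- Residual variance after adding the baseline value = (1 − rho²) times the original.

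Example with rho = 0.5, d = 0.5, n = 32: bias = 0.25 SD, bias/SE = 1.00, false-positive rate 17.0%.

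**4. Results.**

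| d | rho | Bias (SD) | False positives, n = 32 | False positives, n = 46 |
|---|---|---|---|---|
| 0 | any | 0 | 5% | 5% |
| 0.2 | 0.3 | 0.06 | 5.7% | 6.0% |
| 0.2 | 0.5 | 0.10 | 6.9% | 7.7% |
| 0.2 | 0.7 | 0.14 | 8.7% | 10.3% |
| 0.5 | 0.3 | 0.15 | 9.2% | 11.1% |
| 0.5 | 0.5 | 0.25 | 17.0% | 22.4% |
| 0.5 | 0.7 | 0.35 | 28.8% | 38.9% |

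**5. Precision.** The residual variance factor is 0.91, 0.75 and 0.51 for rho of 0.3, 0.5 and 0.7. At rho = 0.5 the gain equals 1/0.75 = 1.33 times the patients. This gain is available when d = 0. It would be smaller where age and fracture type already explain part of the variation, or where surgery weakens the link between the initial and the 1-year value.

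**6. Scope.** The formulas suit measured quantities: radial inclination, volar tilt, ulnar variance and the size of a step or gap. For the mere presence of a step or gap the direction of the argument is the same, but these figures do not apply.

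**The case against.** **The list is open.** The word notably introduces examples, and this is a condensed article whose full protocol and analysis plan are not shown. A reader might infer that the 1-year models will adjust for age and fracture type only; the text does not say that. This stands. But an open list does not commit the study to baseline deformity, and the rule that is stated carries one common set to all secondary outcomes.

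**The panel is there to limit this confounding.** Six surgeons, blinded to treatment and origin, judge the same films, and only disputed cases enter. The article also relies on allocation by hospital and surgeon on call, and its Discussion expects little confounding. A reader might infer that initial displacement will be reported as a treatment effect. The documents do not support that: it needs an imbalance that survives both the panel and the adjustment. The panel makes a large imbalance less likely but does not guarantee balance.

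**Fracture type may already capture displacement.** The article names no classification, so this cannot be settled either way. Whatever fracture type captures reduces the figures above.

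**The size is assumed.** This is correct. The common slope also matters. If deformity carries over only in cast patients, and the arms are equal in size, the bias against the average effect over both groups is rho × d / 2, or 0.03 to 0.175 SD over the same range. Against the effect in cast patients it is zero. No figure in degrees or millimetres can be supported from the documents.

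**The 1-year film.** Table 1, as extracted, ticks X-rays only at first presentation and 6 weeks, while Radiological Outcome also has them at 12 weeks and 1 year. That conflict concerns the outcome film and should be reconciled separately. It does not affect the existence of the baseline film.

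**Conclusion.** The point holds as a cheap improvement to the analysis of secondary outcomes. The named covariates do not include initial radiographic deformity, although allocation is by surgeon choice and a first-presentation film is scheduled for each patient. The 1-year alignment comparison may be biased if displacement still differs between groups after selection and adjustment. The bias is zero under balance and 0.06 to 0.35 SD for the assumed ranges of rho and d. At 32 per group the corresponding false-positive rate is 5.7% to 8.7% at d = 0.2, and 9.2% to 28.8% at d = 0.5. These figures show scale only: rho and d are assumptions, the contribution of age and fracture type is ignored, and a common slope is used. The precision argument does not depend on imbalance.

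The 12-week PRWE analysis, the noninferiority conclusion and the sample size are untouched. The point does not extend to union, which has no corresponding measurement at presentation.

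**What to change.** Measure radial inclination, volar tilt, ulnar variance and articular step or gap on the existing first-presentation film, with the same method and readers as at 1 year. Where several early films exist, specify the one taken before any reduction, so that the covariate is not itself affected by treatment. In Statistical Analysis, state that each parameter's own first-presentation value enters its 1-year regression, in addition to age and fracture type. Fix this before the 1-year radiological data are analysed.

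The cost is reading about 92 existing films and adding one covariate per model. No extra baseline imaging, visits or patients are needed. If the full protocol or analysis plan already lists these covariates, a sentence saying so is enough.
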